### **8.2 AEs, SAEs and SUSARs**

#### **8.2.1 Adverse events (AEs)**

Adverse events are defined as any undesirable experience occurring to a subject during the study, whether or not considered to be related to the investigational product, trial procedure or the experimental intervention. All adverse events reported spontaneously by the subject or observed by the investigator or his staff will be recorded and reported to the sponsor.

We don't expect any adverse events due to the lighting intervention as it is thoroughly tested by Signify test centres and an independent party. Although very unlikely, exposure to the desk-based lighting device might result in discomfort (e.g. visual discomfort or eyestrain, headaches/migraines, or physical complaints due to working at the side of the desk). Blood sampling might lead to distressing effects or increased work pressure might arise as a result of the time investment needed on providing data for the research. All AE's will be registered by the responsible investigator. Participants can contact the investigator or leave any comments/feedback/complaints in all of the questionnaires in the study

(weekly). In case any AE's occur that need action, the responsible researcher will contact the participant (if he/she did not do that him/herself) and discuss whether the study should be discontinued. Reference to the participant's general practitioner is advised in case of physical complaints that need medical evaluation. At the start of the study, participants will receive a letter for their general practitioner with information regarding the study and a contact telephone number and e-mail at which they can reach the responsible researcher for more information. Participants can take this letter to their general practitioner if needed.

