### 3. STUDY DESIGN

A pilot study with a between-subjects manipulation is proposed for the current study design. The type of light (artificial UVB supplementation vs. no artificial UVB supplementation) is manipulated between subjects. In both the intervention group and the control group, repeated measures are employed during a sampling period of 8 weeks. When possible, randomization over the two groups will be conducted (see section 5.2 for more information). Figure 1 gives a graphical representation of the study design.

[figure not shown]

**Figure 1.** Graphical representation of the study design

For the primary objective, the serum 25(OH)D will be investigated. At the start of the study (day 0), participants will be asked to donate 4 ml blood to determine the baseline 25(OH)D levels in their blood. Subsequently, the light intervention is installed at the desks in the home office of participants in the intervention group delivering the ultra-low dose of UVB during daytime. The control group will not be exposed to artificial UVB radiation and will not receive a lamp at their desk.

The blood sampling and serum 25(OH)D analyses will be repeated in Week 4 and Week 8 on pre-scheduled morning time slots, preferably the same day for all participants, and is conducted by Diagnostiek Voor U (DVU) as a formally recognized health-care provider.

The self-reports on food intake (only vitamin D related), subjective sleep timing and quality, and general levels of fatigue will be investigated through (validated) questionnaires. Both the control and intervention group will receive the questionnaires electronically (via LimeSurvey) in the mornings during which blood sampling is also conducted. The second and third questionnaire contains an option for the participant

to give any comments or feedback about the study (procedure and intervention) to gain some additional insight in their study experience. Table 1 gives an overview of the frequency and timing of the data assessments. These assessments are all conducted in both groups.

**Table 1** Overview of the frequency and timing of the different questionnaires and serum 25(OH)D level measurements

|                                                      | Day 0 | Day 29-31 | Day 58-60 |
|------------------------------------------------------|-------|-----------|-----------|
| General information                                  | X     |           |           |

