| Serum 25(OH)D                                        | X     | X         | X         |
| Sleep timing and quality (based on [44 and [45])     | X     | X         | X         |
| General fatigue → Checklist Individual Strength [43] | X     | X         | X         |
| Food intake (vitamin D related), based on [46]       |       |           |           |
| Feedback/comments (optional)                         |       | X         | X         |

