### 3.1 Duration of the study

The study protocol consists of a baseline measurement (Day 0 ) and an 8-week intervention period. Three data assessments will be conducted in day 1 of week 0, day 29-31 of week 4 and day 58-60 of week 8. Each data assessment is expected to take about 20-30 minutes. In addition to these three measurement points, participants are asked to complete a short (<1 minute) diary each day about desk presence, time spent outside, and clothing. The study is scheduled for autumn or winter 2020. This season has been chosen as both serum 25(OH)D and outdoor UV intensity start to decline rapidly to negligible values in this period [39,40].

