| Other, namely                                                                    |                       |                       |                       |                       |                       |                       |                       |                       |                       |                       |
| To be filled in by study manager                                          |                       |                       |                       |                       |                       |                       |                       |                       |                       |                       |
| % occupation                                                                     |                       |                       |                       |                       |                       |                       |                       |                       |                       |                       |
| %BSA                                                                             |                       |                       |                       |                       |                       |                       |                       |                       |                       |                       |
| % time natural UV-B                                                              |                       |                       |                       |                       |                       |                       |                       |                       |                       |                       |

**Figure 7:** Example of the diary to be filled in daily

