### **7.5 Withdrawal of individual subjects**

Subjects can leave the study at any time without giving a reason if they wish to do so without any negative consequences. In the event that a subject stops before data assessment week 4, an attempt will be made to recruit a new volunteer (if available) who can start his/her first measurements in week 4.

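### Section 8.2.1 promises a complaint field in every questionnaire, weekly, but section 3 and Table 1 place one only at weeks 4 and 8, and the diary shows none

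*Protocol*

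**What the plan says.** Section 8.2.1 of the Protocol requires every adverse event that is reported spontaneously or observed by staff to be recorded. It then names two routes for participants. They can contact the investigator, or they can "leave any comments/feedback/complaints in all of the questionnaires in the study". The frequency follows directly: "weekly). In case any AE's occur that need action".

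Section 3 describes the comment field differently: "The second and third questionnaire contains an option for the participant". The purpose that section 3 states for this option is "to give any comments or feedback about the study (procedure and intervention) to gain some additional insight in their study experience". The row "Feedback/comments (optional)" in Table 1 agrees with section 3. It is blank at Day 0 and marked at Day 29-31 and Day 58-60.

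The only weekly instrument in the Protocol is the LimeSurvey upload of the diaries. Section 3.1 gives the content of the diary: "participants are asked to complete a short (<1 minute) diary each day about desk presence, time spent outside, and clothing". Sections 7.1.2 and 7.4.1.3 list the same content. The form in Figure 7, captioned "Example of the diary to be filled in daily", has rows for desk presence, time outside and exposed body areas. Its one free-text line belongs to the body-area block.

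Section 7.5 allows a participant to leave at any time without a reason, and it makes provision for a replacement: "In the event that a subject stops before data assessment week 4". It describes no question to be asked at exit.

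**The concern.** The safety section and the design section describe different things. A team that builds the surveys from section 3 and Table 1 provides an optional feedback box twice. A team that builds them from section 8.2.1 provides one every week. Section 3 also presents the box as a way to learn about the study experience, not as a means of collecting adverse events.

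The complaints that section 8.2.1 considers possible are mild ones: visual discomfort or eyestrain, headache, physical complaints from sitting at the side of the desk, and distress from blood sampling. A routine prompt is more likely to bring out such complaints than reliance on the participant to make contact. Section 8.2.1 also has the researcher contact the participant when an event needs action. A weekly field could trigger that contact. A field that first appears at Day 29-31 cannot do so in time for an earlier event.

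**Working it through.** The point rests on comparing passages. No sample size, power or event rate enters it, and the Protocol gives no figure to reproduce.

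**Where a written complaint field is described**

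| Occasion | Section 8.2.1 | Section 3 and Table 1 | Diary text and Figure 7 |
|---|---|---|---|
| Day 0 questionnaire | yes (all questionnaires) | blank | not applicable |
| Weekly, weeks 1 to 8 | yes (weekly) | upload not listed | no field shown |
| Day 29-31 questionnaire | yes | yes | not applicable |
| Day 58-60 questionnaire | yes | yes | not applicable |

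**Count of occasions**

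- Section 8.2.1, read with the weekly upload: 8 weekly + 3 main = 11, approximately, since the text does not number them.
- Section 3 and Table 1: 2.
- Participant who leaves before Day 29-31, if only the section 3 field is built: 0.

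**Timing of the first occasion**

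- Table 3 (section 10.4.2) gives 40 daily diaries over 8 weeks, so 40 / 8 = 5 per week.
- By the end of week 4, 4 × 5 = 20 diary days have passed, and 20 / 40 = 50%.
- Under section 3, the first written opportunity therefore comes about halfway through the study period. Lamp exposure before that point is slightly shorter, because the lamp is installed only after the Day 0 blood result is known (section 7.4).

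**What this does to an event in the first four weeks, through this route**

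- The participant is still in the study at Day 29-31: the event can be written down then, late and from recall.
- The participant has left before Day 29-31: the event cannot be reported through this route.
- The participant leaves between weeks 4 and 8: the same holds for events after the week 4 questionnaire.

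**Other routes from the first lamp day**

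- Direct contact, spontaneous report and staff observation (section 8.2.1).
- A contact person for lamp questions (section 6.2).
- The instruction to report skin redness or eye strain (section 12.2). It is one of the luminaire guidelines and refers to the user manual. Section 7.4 gives a manual to those who receive a lamp, so this route is not shown to exist for controls.
- The regular irradiance check by a technically trained person (section 12.2). It could allow observation in the lamp arm, but the text does not say that complaints are asked about.

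Apart from staff observation, each of these needs the participant to act first.

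**The case against.** The strongest reply is that the weekly field may well exist. Table 1 does not list the diary or the upload at all, so its silence says nothing about the upload page. Section 3 does not say that only the second and third questionnaires carry a comment option. Figure 7 is labelled an example. Section 10.5 treats the weekly upload as a questionnaire, which fits the word weekly in section 8.2.1. The questionnaires themselves are in a separate file that is not part of this document. All of this stands: the weekly field is unsupported by the rest of the Protocol, but it is not shown to be absent. The one direct clash is Day 0, which comes before the lamp is installed and so does not matter for lamp-related events.

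A reader might also infer that first-month events are lost. The document does not support that. Anyone still in the study can report them at Day 29-31, and the other routes are open throughout. The loss through this field is confined to people who leave.

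A reader might further infer that the safety conclusion is biased towards no events. That does not follow either. The objectives, the endpoints and section 9 contain no safety endpoint and no comparison of events between groups, and the Protocol gives no event or dropout rate from which a bias could be sized.

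Finally, it can be said that one corrected sentence would settle the text. That is true as editing. It would, however, mean dropping the weekly rule that the safety section itself sets.

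**Conclusion.** The point holds as an inconsistency in how adverse events are collected, with a modest practical consequence. Section 8.2.1 states a weekly written route. No other part of the Protocol provides it, and section 3 with Table 1 provides a field on two occasions, the first about halfway through the 8 weeks.

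The consequence is conditional on the surveys being built from section 3 and Table 1 alone. In that case mild events before week 4 reach the team through this route late and by recall, and they do not reach it through this route from anyone who leaves before week 4. How many events or leavers that would affect cannot be estimated from the Protocol. The counts above are of reporting occasions, not of missed events.

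**What to change.** Reconcile section 8.2.1 with section 3 and Table 1 by keeping the weekly rule:

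1. Add one short item to the weekly LimeSurvey upload, the same in both arms: whether there was any skin, eye, headache or other complaint that week (yes or no), with a text box.
2. Describe the item in section 3 and add a row to Table 1 for the weekly upload, so that the schedule matches section 8.2.1.
3. Ask the same item once of anyone who leaves early, as a voluntary question, and say so in section 7.5.

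No comment field is needed at baseline, because the lamp is installed after Day 0. The wording of section 8.2.1 can be limited to the weekly upload and the second and third main questionnaires.

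The cost is a few seconds per participant per week on a form that is already sent, and a little more time for the investigator to review what comes in. A prompted item will probably bring out more minor complaints than spontaneous reporting would, so the report should state how events were collected.

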### **8.2.2                      *Serious adverse events (SAEs)***

We do not expect SAEs from this study. In case they will occur, they will be reported as described below.

A serious adverse event is any untoward medical occurrence or effect that

- results in death;
- is life threatening (at the time of the event);
- requires hospitalisation or prolongation of existing inpatients' hospitalisation;
- results in persistent or significant disability or incapacity;
- is a congenital anomaly or birth defect; or
- any other important medical event that did not result in any of the outcomes listed above due to medical or surgical intervention but could have been based upon appropriate judgement by the investigator.

An elective hospital admission will not be considered as a serious adverse event.

The responsible investigator will report all SAEs to the sponsor without undue delay after obtaining knowledge of the events.

The sponsor will report the SAEs through the web portal *ToetsingOnline* to the accredited METC that approved the protocol, within 7 days of first knowledge for SAEs that result in death or are life threatening followed by a period of maximum of 8 days to complete the initial preliminary report. All other SAEs will be reported within a period of maximum 15 days after the sponsor has first knowledge of the serious adverse events.

### **8.2.3                      *Suspected unexpected serious adverse reactions (SUSARs)***

Not applicable.

### **8.3 Annual safety report**

Not applicable.

### **8.4 Follow-up of adverse events**

All AEs will be followed until they have abated, or until a stable situation has been reached. Depending on the event, follow up may require additional tests or medical procedures as indicated, and/or referral to the general physician or a medical specialist. SAEs need to be reported till end of study within the Netherlands, as defined in the protocol (section 6.2.2.).

### **8.5 Data Safety Monitoring Board (DSMB) / Safety Committee**

The WMO requires on-site monitoring for drug related research conform the ICH-GCP regulation (2005/28 EG). However, in case the clinical trial is not related to drugs and still WMO obligatory, monitoring is not legally required. The intervention of the proposed clinical trial is a lighting intervention and not a drug. Therefore, a request for exemption will be made.

## 9. STATISTICAL ANALYSIS

The data analyses consist of multiple steps. All data will be presented quantitatively.

As a first step, we will inspect the distribution of the variables of interest. A Shapiro-Wilk test will be conducted to inspect normality of the variables. If needed and possible, a transformation of the scores will be performed to adhere to the assumption related to normality for the statistical analyses. Subsequently, an outlier detection will be performed with outliers determined as values more than 3 SD's from the mean.

Next, we will provide the descriptive statistics for the experimental and control condition for the variables measured only at baseline (see Table 1), as well as for the dependent variables (i.e., the variables for the primary (serum 25(OH)D) and exploratory research objectives (fatigue and sleep), see Section 2.) for each of the measurement points. Comparisons of the variables at baseline will be investigated via independent samples T-test to examine whether there were significant differences between the two groups for any of the variables at measured baseline. If the data appears to be not normally distributed and no transformation is applicable, we will employ a non-parametric test (Mann-Whitney test).

Subsequently, the main research objective (i.e., effects of the light intervention on serum 25(OH)D at week 8) will be investigated using an ANCOVA analyses with the intervention (yes/no) as predictor and change scores in serum 25(OH)D as outcome variable. This analysis will further be controlled for average desk presence and time spent outside. In case data is non-normally distributed a non-parametric test (Mann-Whitney test) will be conducted taking into account the limitation that this analysis cannot control for the mentioned confounders. Analyses will only be conducted with data from participants with both the baseline measurement and the final measurement point available. An alpha level of 0.05 will be used as criterion.

After that, an explorative Linear Mixed Model (LMM) analysis will be conducted to examine changes in serum 25(OH)D over time (i.e., first and second measurement, using baseline scores as a control variable). LMM analyses will be executed because this type of analysis takes into account dependency of the data due to the repeated measures as well as potential missing values at any of the measurement points. In case a significant Intervention \* Measurement interaction is found ( $p < 0.05$ ), post-hoc comparisons are conducted to investigate differences between the intervention and control group at each of the two measurement points. In addition, we will conduct an exploratory LMM analysis in which we investigate the correlation between UVB dose (calculated based on desk presence and clothing) and serum 25(OH)D over time to examine whether there are large differences in these values based on the UVB dose participants received. These explorative analyses will also be controlled for time spent outside during daytime.

Last, exploratory LMM analyses will be conducted to investigate relations between the variation in serum 25(OH)D and variations in sleep duration, sleep quality, and general feelings of fatigue.

This will be established by running a LMM model with serum 25(OH)D as well as measurement point as predictor in order to account for changes in sleep patterns or fatigue levels over time. For visual inspection purposes, this will also be investigated separately in both the intervention and the control

group. This will be analyzed in this way due to a lack of blinding in participants which may create bias when directly investigating the effect of the intervention on fatigue/sleep.

